### Study outcomes

The primary outcome is the incidence of preeclampsia and/or small for gestational age (SGA) <5^th^ customised birthweight centile [46]. Preeclampsia will be defined as new onset hypertension (systolic BP ≥140 mmHg and/or diastolic BP ≥90 mmHg) arising after 20 weeks gestation with evidence of significant proteinuria (dipstick proteinuria (≥1+) subsequently confirmed by spot urine protein/creatinine ratio ≥ 30 mg/mmol and/or 24 h urine protein excretion >0.3 g) or any multi-system complication including haematological, liver, renal and neurological involvement [47]. IUGR is difficult to define and measure and so SGA defined by customised birthweight centiles will be used as the most reproducible surrogate. Customised centiles adjusting for infant sex, gestation at delivery and maternal variables—parity, ethnicity, height and weight will be used [46]. The key secondary study outcomes are shown in Table 1.

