### Inclusion criteria

Women are eligible for the trial if they are >6^+0^ and <16^+0^ weeks gestation with fetal viability and a singleton pregnancy confirmed on ultrasound scan and at risk of preeclampsia and/or IUGR based on their past obstetric history. This is defined by (1) previous preeclampsia delivered <36^+0^ weeks in their last on-going pregnancy reaching >12 weeks, (2) previous SGA < 10^th^ customised birthweight centile delivered <36^+0^ weeks in their last ongoing pregnancy reaching >12 weeks with no major fetal anomaly or, (3) previous SGA ≤ 3^rd^ customised birthweight centile delivered at any gestation in their last on-going pregnancy reaching >12 weeks with no major fetal anomaly.

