### Exclusion criteria

Women are not eligible for the trial if they have (1) any contraindication to LMWH use, (2) a requirement for LMWH use such as previous thrombosis, APS, (3) previous successful pregnancy with LMWH treatment, (4) multiple pregnancy, (5) known pre-existing type 1 or 2 diabetes or renal disease (with serum creatinine >150), (6) thrombocytopenia (platelet count <80 × 10^9^/L) prior to randomisation or (7) a known major fetal anomaly/chromosomal abnormality.

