### Sample size

We have estimated a risk of recurrence of preeclampsia and/or SGA < 5^th^ customised centile for the included population of 25% when managed routinely with aspirin (and calcium). A trial of 160 participants, allowing for a 5% drop-out/early miscarriage rate will have 80% power at a two-sided significance level of 0.05 to detect a difference between 25 and 7% [37].

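### The preeclampsia component requires new-onset hypertension after 20 weeks, but women already hypertensive are eligible, so superimposed preeclampsia without SGA <5th centile goes uncounted

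*Protocol article*

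**What the plan says.** All places are in the protocol article.

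- **Study outcomes, composite.** "The primary outcome is the incidence of preeclampsia and/or small for gestational age (SGA") below the 5th customised centile. Either component makes a woman an event.
- **Study outcomes, preeclampsia.** "Preeclampsia will be defined as new onset hypertension (systolic BP ≥140 mmHg and/or diastolic BP ≥90 mmHg) arising after 20 weeks gestation". To this must be added confirmed significant proteinuria "or any multi-system complication including haematological, liver, renal and neurological involvement".
- **Inclusion criteria.** Women enter because they are "at risk of preeclampsia and/or IUGR based on their past obstetric history". The three routes are earlier preeclampsia delivered before 36 weeks, earlier SGA <10th centile delivered before 36 weeks, and earlier SGA at or below the 3rd centile at any gestation. No blood pressure condition applies at entry.
- **Exclusion criteria.** Among medical conditions the list names "known pre-existing type 1 or 2 diabetes or renal disease (with serum creatinine >150"), thrombocytopenia and conditions that require LMWH. Pre-existing hypertension is not on it.
- **Sample size.** The control risk is given "for the included population of 25% when managed routinely with aspirin (and calcium"), with "80% power at a two-sided significance level of 0.05 to detect a difference between 25 and 7"%.

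The article nowhere mentions chronic hypertension or superimposed preeclampsia.

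**The concern.** The stated outcome rule does not fit the population that the stated criteria admit. Hypertension that was present before 20 weeks cannot be of new onset after 20 weeks. A woman with chronic hypertension who develops new proteinuria or organ involvement therefore fails the preeclampsia definition as written, although she has the condition the trial aims to prevent.

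The effect reaches beyond the primary outcome. Six key secondary outcomes in Table 1 use the same term: the four combined outcomes, preeclampsia, and severe preeclampsia. For preeclampsia and severe preeclampsia on their own, an SGA infant does not bring the case back into the count. For the outcome that requires both preeclampsia and SGA <10th centile, it does not help either.

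There is a smaller mirror-image gap. The proteinuria limb asks for significant proteinuria and does not say new proteinuria. Renal disease is excluded only above a creatinine of 150, so a woman with milder disease and existing proteinuria can enter. If her blood pressure rises after 20 weeks, she meets the definition with no change in her urine.

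Two things are at stake: some lost events, and a classification left to judgement. Under Study groups, participants, clinicians and investigators all know the allocation. Outcome data are collected from clinical records. Where the written rule does not fit a patient, sites may fill the gap differently and with knowledge of the arm.

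**Working it through.** **1. The text.** The definition joins its parts as new-onset hypertension *with* proteinuria or a multi-system complication. The second part is an added requirement, not a second route. Reading organ involvement as sufficient without hypertension would make any such complication preeclampsia, which is not plausible. The table applies the definition to a woman hypertensive before 20 weeks.

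| What happens after 20 weeks | Preeclampsia component | Primary outcome |
|---|---|---|
| New proteinuria or organ involvement, infant not SGA <5th | not met | non-event |
| New proteinuria or organ involvement, infant SGA <5th | not met | event, through SGA |
| Neither, infant SGA <5th | not met | event, through SGA |

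Only the first row is lost from the primary outcome.

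**2. The plan's own sample size.** Inputs from Sample size: p1 = 0.25, p2 = 0.07, two-sided 0.05, 80% power, 5% drop-out. Equal arms are assumed, as in the interim analysis section.

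n = [1.96·√(2·p̄·(1−p̄)) + 0.8416·√(p1(1−p1) + p2(1−p2))]² / (p1−p2)², with p̄ = 0.16

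= [1.96·√0.2688 + 0.8416·√0.2526]² / 0.18² = 63.9, so 64 per arm.

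With continuity correction: (63.9/4)·[1 + √(1 + 4/(63.9·0.18))]² = 74.6, so 75 per arm and 150 in total. Then 150/0.95 = 158, against 160 stated. The figure reproduces and is not in dispute.

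**3. Size of the undercount.** The documents give no prevalence, so these are assumptions:

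- h, share of women with chronic hypertension: 5-15%
- r, their share of events relative to their number: 1 to 1.5
- q, share of their events that are preeclampsia without SGA <5th centile: 40-70%

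Fraction of all true events uncounted: m = h·r·q. Counted rates: p1(1−m) and p2(1−m). With 5% drop-out, 160·0.95 = 152, or 76 per arm.

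Power = Φ{[(p1−p2)·√76 − 1.96·√(2·p̄·(1−p̄))] / √(p1(1−p1) + p2(1−p2))}

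| Scenario | m | Counted rates | Risk ratio | Difference | Power, 76 per arm |
|---|---|---|---|---|---|
| As planned | 0 | 25.0% vs 7.0% | 0.28 | 18.0 points | 86.4% |
| Mild: 0.05·1·0.4 | 0.020 | 24.5% vs 6.9% | 0.28 | 17.6 points | 85.6% |
| Severe: 0.15·1.5·0.7 | 0.1575 | 21.1% vs 5.9% | 0.28 | 15.2 points | 78.7% |

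Events lost across both arms: 76·(0.25 + 0.07)·m = 24.3·m, which is 0.5 to 3.8 women.

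**4. Which power scale.** The 86% uses no continuity correction, whereas the stated 160 reproduces only with it. On the corrected scale, replace 76 by 76·[1 − 1/(76·(p1−p2))]². This gives an effective 65.3, 65.1 and 63.4 per arm for the three rows, and power of 81%, 80% and 71%. The starting level differs, but the drop is similar: at most about 8 points on one scale and 10 on the other.

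**The case against.** **The composite limits the damage.** A reader might infer that superimposed preeclampsia can never count, or that these women cannot have an event. The documents do not support that. SGA <5th centile is a sufficient component, so only cases without it are lost from the primary outcome. Any estimate that treats every superimposed case as lost is too high.

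**The treatment effect need not be diluted.** A reader might infer that the effect shrinks towards the null. If events are missed in the same proportion in both arms, the risk ratio stays at 0.28 and only the absolute difference and power fall. Randomisation should balance these women on average, so systematic bias is not shown. This objection stands.

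**The 25% is not undermined.** It is stated as the risk of the trial's own outcome in its own population, and nothing shows that superimposed cases were included in it. Nor do the documents say that chronic hypertension marks the women most likely to recur. The Background ties recurrence to how early and severe the previous disease was. The point needs neither claim.

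**The article is condensed and cites a reference for the definition.** That source is not at hand and may treat superimposed disease separately. However, the article gives the definition in operational detail, with thresholds, gestation, confirmatory tests and organ systems, and brings in no superimposed category. This is a stated rule that does not fit the stated population, so it is more than detail left to the full protocol.

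**A restricted outcome is a legitimate choice.** That is so, but the article describes the restriction as limiting the composite to preeclampsia and SGA. It does not state an intention to leave out superimposed disease.

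**The proteinuria gap is narrow.** Such a woman still needs new hypertension after 20 weeks. The gap adds events and cannot be sized from the documents. It deserves a clarifying word and carries no weight in the numbers.

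**Conclusion.** The concern holds for the preeclampsia component. As written, superimposed preeclampsia without SGA <5th centile is a non-event for the primary outcome, and superimposed preeclampsia of any kind falls outside the Table 1 outcomes of preeclampsia and severe preeclampsia.

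The size is small to modest. Under the stated assumptions, 0.5 to 3.8 of about 24 expected events go uncounted, and power falls by about 1 to 8 points (1 to 10 with continuity correction). The risk ratio is unchanged if undercounting is proportional. The size rests wholly on assumed prevalence and overlap. The mismatch between eligibility and definition rests on the text alone.

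The better reason to act is that the classification of these women is left open in an unblinded trial. That is a risk of inconsistent adjudication, and the documents do not show that any bias arises from it.

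**What to change.** Amend the definition under Study outcomes in three respects:

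1. In women hypertensive before 20 weeks, count superimposed preeclampsia when new significant proteinuria or one of the listed multi-system complications arises after 20 weeks.
2. State that the proteinuria limb means new proteinuria.
3. Apply the same rule in both arms and to every Table 1 outcome that uses the term.

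Fix the wording before any outcome data are reviewed by arm, and so before the interim analysis. Because everyone knows the allocation, a later change would be open to the charge that it was made with the results in view.

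Cost: no additional participants or visits, but some classification work from clinical records. That work depends on early-pregnancy blood pressure and urine results being in those records. The article's text does not list them as trial measurements, and its schedule figure is not shown, so their availability should be checked first.

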### Sample size

We have estimated a risk of recurrence of preeclampsia and/or SGA < 5^th^ customised centile for the included population of 25% when managed routinely with aspirin (and calcium). A trial of 160 participants, allowing for a 5% drop-out/early miscarriage rate will have 80% power at a two-sided significance level of 0.05 to detect a difference between 25 and 7% [37].

### Data monitoring committee (DMC) and interim analysis

An independent DMC comprising of a statistician, obstetrician, and obstetric physician with clinical trials experience will review serious adverse events. They will review the results of an interim analysis once 98 participants have been recruited and completed pregnancy. A study group of 49 participants in each arm will have 80% power at a two-sided significance level of 0.05 to detect a difference between 25 and 4%. The DMC will report to the trial investigator group and may advise discontinuation of the trial if there is an excess of serious adverse events in the LMWH treatment group or if a significant benefit is already demonstrated. Results of the interim analysis will only be known to members of the DMC and the trial investigator group. Responsibility for early discontinuation of the trial will ultimately rest with the trial investigator group.

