Subsequently a number of randomised controlled trials have been reported. Initial trials focussed specifically on populations with or without thrombophilia, believing that the risk of these placental diseases may be significantly different between the groups and may respond differently to intervention with heparin or LMWH. In 2009, Rey et al. reported the outcomes of a randomised trial of LMWH in women with a past history of placental mediated problems (including preeclampsia and IUGR) and no thrombophilia. This trial demonstrated a large reduction in the primary composite outcome (severe preeclampsia, birthweight <5th centile, major abruption or fetal death after 20 weeks) 5.5 vs 23.6% adjOR 0.15, 95% CI 0.03–0.70 [37]. However the study was halted after just over one third of the planned participants had been recruited (results of 110 participants analysed of a planned sample size of 276 women). The FRUIT-RCT reported similar promising outcomes associated with LMWH use for women with inherited thrombophilia, demonstrating a significant reduction in the recurrence of hypertensive disease (preeclampsia, HELLP syndrome and/or eclampsia) <34 weeks gestation, 8.7 vs 0% risk difference 8.7, 95% CI 1.9–15.5%) [38]. This study also did not complete recruitment of initial planned sample size (139 of 262).

Subsequent published trials including the ‘Heparin in pregnant women with adverse pregnancy outcome to improve rate of successful pregnancy’ (HAPPY) Study [39], the ‘Prevention of maternal and perinatal complications by enoxaparin in women with previous severe preeclampsia’ (HEPEPE) Study [40] and the ‘Thrombophilia in Pregnancy Prophylaxis Study’ (TIPPS Study) [41] have failed to demonstrate any improvement in outcome with LMWH.

All of these trials have had prolonged recruitment phases (up to 12 years [41]) and have been difficult to recruit to. Several trials have stopped early due to recruitment difficulties and for perceived overwhelming effect [37] or futility after interim data analysis [39]. Of note, these previous randomised controlled trials have had broad inclusion criteria and diverse composite outcome measures.

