### Data analysis

All data will be collected and stored under de-identified study ID. Data will be analysed by an independent statistician. Population characteristics between the groups will be compared initially to identify any potential confounding variables. Data will be analysed on an intention to treat basis comparing primary and secondary outcomes in both groups. Analyses will make adjustment for recruiting site and thrombophilia status. *P*-value <0.05 will be considered significant.

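### The efficacy interim and the final analysis both use an unadjusted two-sided 0.05, so the stated 5% is not assured: about 6.4–6.5% overall if the interim can stop only for benefit

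*Protocol article*

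**What the plan says.** Three sections of the protocol article bear on this.

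- **Data monitoring committee (DMC) and interim analysis.** On timing: "They will review the results of an interim analysis once 98 participants have been recruited and completed pregnancy". On size: "A study group of 49 participants in each arm will have 80% power at a two-sided significance level of 0.05 to detect a difference", the rates being 25% and 4%. The committee may advise discontinuation for an excess of serious adverse events in the enoxaparin group, "or if a significant benefit is already demonstrated". The trial investigator group sees the interim results and takes the final decision.
- **Sample size.** "A trial of 160 participants, allowing for a 5% drop-out/early miscarriage rate" is said to give "80% power at a two-sided significance level of 0.05 to detect a difference between 25 and 7"%.
- **Data analysis.** Analyses adjust for recruiting site and thrombophilia status, and a P-"value <0.05 will be considered significant".

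No other significance level appears. The article gives no stopping boundary, alpha spending or reduced final threshold.

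**The concern.** The primary hypothesis is given two chances at 0.05: once at 98 completed pregnancies and again at the end. Unless the interim level is made stricter, or both levels are lowered, the chance of at least one false positive exceeds the 5% that the Sample size and Data analysis sections state.

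A lenient early stop also tends to exaggerate the effect. If the true rates were 25% and 15%, an uncorrected chi-square test at the interim would cross for benefit about 24% of the time. The mean observed difference in those trials would be about 20 points, against a true 10 (with Fisher's test the crossing rate is about 17%).

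The Background describes this kind of history. An earlier trial, which is also the reference for the sample size, was halted with 110 of a planned 276 women analysed and a large effect, and later trials did not show an improvement. The Discussion intends the present results to feed meta-analyses.

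**Working it through.** **Inputs.** Interim: 98 women, 49 per arm, 25% against 4%, two-sided 0.05 (interim section). Final: 160 women less 5%, which is 160 × 0.95 = 152, or 76 per arm; 25% against 7%, two-sided 0.05 (Sample size). Final threshold P<0.05 (Data analysis).

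**Step 1: reproduce the plan's own figures.**

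- *Final size.* n = [1.96·√(2p̄q̄) + 0.842·√(p₁q₁ + p₂q₂)]² / (p₁ − p₂)². With p̄ = 0.16, this is [1.96·√0.2688 + 0.842·√0.2526]² / 0.18² ≈ 64 per arm. The continuity correction raises it to 75 per arm, or 150 in total, and 150/0.95 ≈ 158, against 160 stated.
- *Interim power.* The exact power of Fisher's test with 49 per arm, 25% against 4%, at two-sided 0.05 is 80.2%, which matches the stated 80%. The uncorrected chi-square test would give 89.8%.

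Both figures reproduce with the full 0.05, so the sizing shows no sign of alpha held back for the second look.

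**Step 2: overall error with 1.96 at both looks.** Under the null, (Z₁, Z₂) is bivariate normal with correlation √t, where t is the information fraction. t = 98/152 = 0.645 gives √t = 0.803; t = 98/160 = 0.6125 gives √t = 0.783.

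| Event under the null | t = 98/152 | t = 98/160 |
|---|---|---|
| False claim of benefit: Z₁>1.96 or Z₂>1.96 | 3.9% | 4.0% |
| Benefit-only interim stop, two-sided final: Z₁>1.96 or abs(Z₂)>1.96 | 6.4% | 6.5% |
| Either direction at both looks: abs(Z₁)>1.96 or abs(Z₂)>1.96 | 7.8% | 7.9% |

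The rows agree with each other. Adding the 2.5% final-look error in the harm direction to 3.9% gives 6.4%, and doubling 3.9% gives 7.8%.

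**Step 3: check by binomial simulation** (25% in both arms, 49 then 76 per arm, uncorrected chi-square, 2 million runs). Final look alone: 5.0%. Benefit-only interim: 6.4%. Either direction: 7.8%.

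**Step 4: dependence on the test.** With unadjusted Fisher exact tests at both looks and the same 25% null, the error is about 5.0% counting both directions and 4.1% with benefit-only stopping, and false claims of benefit are about 2.5%. The discreteness of Fisher's test absorbs the extra look. The same dependence shows in a single table: 12/49 against 4/49 gives p = 0.029 by uncorrected chi-square and p = 0.053 by Fisher.

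**Step 5: boundaries that keep 5% overall** (t = 98/152).

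| Rule | Interim p | Final p | Interim power, 25% v 4% (Fisher, 49/arm) | Final-look power, 25% v 7% (Fisher, 76/arm) |
|---|---|---|---|---|
| As printed | 0.05 | 0.05 | 80.2% | 83.2% |
| Haybittle-Peto | 0.001 | 0.0499 | 30.2% | 83.2% |
| Lan-DeMets O'Brien-Fleming, two-sided 0.05 spent | 0.0146 | 0.0445 | 66.1% | 82.2% |

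Spending 0.025 per side instead gives limits of about 0.0105 and 0.0467. With an interim limit of 0.001 and an unchanged final test at 0.05, the total would be about 5.01%. The interim level is therefore what drives the inflation.

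**The case against.** Four points can fairly be made for the plan.

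- **The interim threshold is inferred.** The 0.05 in the interim section belongs to a power statement, and the stopping sentence gives no p-value. A committee charter or analysis plan, neither shown, could set a strict limit. The reply is that 0.05 is the only level printed and is attached to both looks. A stricter limit would have to replace the printed level and, on Fisher's test, the 80% power that goes with it. This is a statement the article fixes, so it is more than a detail left to another document.
- **A reader might infer that the true type I error is about 8%, inflated by more than half.** The protocol does not support that without qualification. The 7.8–7.9% counts an interim crossing in the harm direction, whereas the efficacy stop is worded for benefit only. For that rule the overall figure is 6.4–6.5%, a relative increase of about 28% (6.4/5). An increase of more than half applies to false claims of benefit (3.9/2.5 = 1.56). This objection stands and sets the size reported here.
- **The test matters, and the plan's own sizing points to a conservative one.** The interim power matches Fisher's test and the final size matches the continuity-corrected formula. If such unadjusted tests were used at both looks, the error would be about 4–5%. This stands as a limit. But the Data analysis section plans adjustment for site and thrombophilia status, and the interim test is not named, so that protection cannot be assumed.
- **The stop is advisory.** The percentages are therefore the chance of crossing, and become error rates only if a crossing leads to a stop or a claim. But leaving the decision to an investigator group that sees the results, with no stated limit, does not itself control the error.

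**Conclusion.** The concern holds in a limited form. The article attaches an unadjusted two-sided 0.05 to an interim that can stop the trial for benefit and again to the final analysis, so its stated 5% is not assured. The overall error is about 6.4–6.5%, with false claims of benefit at 3.9–4.0% instead of 2.5%. This rests on three assumptions: the interim limit is the printed 0.05, a significant benefit at the interim leads to a stop or a claim, and the test holds its nominal level. Counting both directions at the interim raises the total to 7.8–7.9%. Conservative unadjusted exact tests at both looks would bring it to about 4–5%. Because the answer depends on choices the article leaves open, while the level it prints is 0.05 at each look, the boundary should be written down before the interim data are seen.

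**What to change.** In the interim section, replace the reference to a significant benefit with a numerical efficacy boundary for the primary outcome, and name the test to which it applies. In the Data analysis section, give the matching final threshold for the primary outcome in place of P<0.05. Either of these would serve:

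- Haybittle-Peto: interim p<0.001, final p<0.0499.
- Lan-DeMets O'Brien-Fleming at 98/152: interim p<0.0146 and final p<0.0445 when two-sided 0.05 is spent, or about 0.0105 and 0.0467 when 0.025 is spent per side. State which convention is used, and recompute the limits if the interim falls at a different information fraction.

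Restate the interim power for 25% against 4% at the chosen limit: by Fisher's test about 30% at 0.001 or about 66% at 0.0146, instead of 80%.

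The cost is wording in two sections and the lower interim power. No participants are added, and final-look power for 25% against 7% at 76 per arm stays at about 82–83%, above the stated 80%.

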### Study groups

Women will be assigned to one of two groups; Group one will receive ‘standard high risk care’ and Group two will receive ‘standard high risk care’ and enoxaparin 40 mg sc (Clexane®, Sanofi-Aventis) [42] daily from recruitment (at gestational age >6^+0^ and <16^+0^ weeks) until 36^+0^ weeks or delivery, whichever occurs sooner.

Standard high risk care is defined as care co-ordinated by a high risk antenatal clinic service, aspirin 100 mg daily until 36^+0^ weeks and calcium 1000–1500 mg daily until 36^+0^ weeks (unless only had previous SGA with no preeclampsia as eligibility criteria). This is an open-label randomised study and all participants, clinicians and investigators will be aware of study group assignment.

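### The plan lets the investigator group of this open-label trial know the comparative interim results, and nothing limits this to a DMC recommendation to stop

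*Protocol article*

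**What the plan says.** Protocol article, Data monitoring committee (DMC) and interim analysis:

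- Timing: "They will review the results of an interim analysis once 98 participants have been recruited and completed pregnancy".
- Grounds for stopping: the DMC "may advise discontinuation of the trial if there is an excess of serious adverse events in the LMWH treatment group or if a significant benefit" has already been shown.
- Power at the interim, for 25% against 4%; the statement begins: "A study group of 49 participants in each arm will have 80% power at a two-sided significance level of 0.05 to detect a difference between".
- Access: "Results of the interim analysis will only be known to members of the DMC and the trial investigator group".
- Authority: "Responsibility for early discontinuation of the trial will ultimately rest with the trial investigator group".

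Protocol article, Study groups: "This is an open-label randomised study and all participants, clinicians and investigators will be aware of study group assignment".

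Three other sections bear on the point. Study outcomes defines preeclampsia by blood pressure thresholds together with either dipstick proteinuria confirmed by a quantitative test or a multi-system complication. Obstetric care and trial procedure leaves care to the local obstetric team. Data analysis assigns the analysis to an independent statistician.

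**The concern.** An independent DMC looks at outcome data by arm so that those who run the trial need not see them while it continues. The access sentence gives up that separation by naming the investigator group as a permitted recipient alongside the DMC.

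In a blinded trial the harm would be limited, because investigators could not connect a trend with an individual woman. Here they know each woman's arm. With the interim trend as well, they could, even without intent, change how closely preeclampsia is looked for, when a woman is delivered, whether a control woman receives LMWH outside the protocol, or who is invited to join. Any such change that differs by arm enters the primary comparison. It could not be removed in the analysis, because nothing would be recorded from which to estimate it.

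**Working it through.** **1. Are the interim results comparative?** Yes. Both stopping grounds, excess serious adverse events in the LMWH group and a significant benefit, compare the arms. The power statement is for a difference of 25% against 4% with 49 women per arm.

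**2. Do the plan's own figures reproduce?** They supply the inputs for step 3.

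- Final sample size. Inputs from Sample size: a control risk "for the included population of 25% when managed routinely with aspirin (and calcium"), and 160 women. The power statement, whose second rate is 7%, begins: "allowing for a 5% drop-out/early miscarriage rate will have 80% power at a two-sided significance level of 0.05 to detect a difference between 25 and". Without continuity correction, n per arm = [1.96·√(2·0.16·0.84) + 0.8416·√(0.25·0.75 + 0.07·0.93)]² / 0.18² = 63.9, so 64. With continuity correction, n per arm = (63.9/4)·[1 + √(1 + 4/(63.9·0.18))]² = 74.6, so 75, or 150 in total. Allowing for 5% loss, 150/0.95 = 158, against the stated 160.
- Interim power. For 49 per arm and 25% against 4%, exact enumeration with Fisher's test gives 80.2%, against the stated 80%.

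Both figures hold. This point corrects no number in the plan.

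**3. How many women could be affected?**

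- Of all randomised women: 160 − 98 = 62, and 62/160 = 38.75%, about 39%.
- Of evaluable women: 160 × 0.95 = 152; 152 − 98 = 54; 54/152 = 35.5%, about 36%. This treats all 98 interim women as evaluable, as the plan's 49 per arm does.

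Both are upper bounds. The trigger is 98 completed pregnancies, and the article states no pause in recruitment. Some of the 62 will therefore already be enrolled, and some may deliver while the interim is analysed and reported. The number still to be recruited is smaller than 62, and the document does not allow it to be calculated.

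**4. What could a shift do?** The document gives no size for one, so this is an illustration under stated assumptions: no true effect, 25% in both arms, 76 evaluable women per arm (49 before and 27 after the interim), the trial continues, and only the enoxaparin arm's recorded rate after the interim moves.

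Pooled enoxaparin rate = (49 × 0.25 + 27 × p)/76. The chance of a false claim of benefit is the normal-approximation power for 25% against that pooled rate, with 76 per arm at two-sided 0.05.

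| Enoxaparin rate after interim (p) | Pooled enoxaparin rate | Spurious difference | Chance of false claim of benefit |
|---|---|---|---|
| 25% | 25.0% | 0 | 2.5% |
| 20% | 23.2% | 1.8 points | about 4.4% |
| 15% | 21.4% | 3.6 points | about 7.5% |

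**5. Does any stated safeguard close the gap?** The independent statistician governs who analyses the data, not who receives the interim results. The article describes no blinded assessment of outcomes, and the access sentence carries no condition.

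**The case against.** The strongest case on the other side has five parts.

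- **The sentence is a ceiling, not a release rule.** It limits who may know the results. It does not say when they are passed on, in what detail, or that data by arm follow a recommendation to continue. This stands. A reader might infer that the investigators receive the results whatever the DMC advises, but the text does not say so. What it does is permit this and set no condition against it.
- **The investigators may not be the treating clinicians.** Local teams give the care, and the article lists clinicians and investigators separately. This stands in part: the overlap is not stated, so influence on care is possible but not established.
- **Much of the outcome is hard to influence.** Customised birthweight centile is largely objective, and preeclampsia has numerical thresholds with a confirmatory test. This narrows the concern but does not remove it. How hard preeclampsia is looked for can still vary, and the timing of delivery is a clinical decision.
- **Open-label knowledge exists from the start.** Only the increment from knowing the trend is at issue, and the documents do not size it. Also, LMWH is not part of control care, and a change in who is approached does not by itself bias the comparison, because it alters both arms. All of this is fair, and it is why the table in the working is only an illustration.
- **The investigators hold the final decision on stopping.** A reader might take that as a second defect, or as a reason why they must see the data. Neither follows. The authority can stay where it is, and using it does not require outcome data by arm while the DMC advises continuing.

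**Conclusion.** The point holds as a rule fixed badly, not as detail missing from a condensed article: the text names the investigator group as a permitted recipient of comparative results and attaches no condition. It is a risk of bias and matters only if the trial continues past the interim. It rests on preeclampsia and the timing of delivery more than on birthweight centile.

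The exposure is at most 62 of 160 women (39%), or about 54 of 152 evaluable (36%). The statement that more than a third of the outcome data will be generated after investigators know the result would go too far, because enrolment and deliveries may continue while the interim is being prepared. The 4.4% and 7.5% in the working depend wholly on assumed shifts.

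No figure in the plan is wrong, and sample size, power and final analysis are unaffected. It should be fixed, and before the interim, because knowledge once released cannot be withdrawn.

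**What to change.** Replace the access sentence in the section on the DMC and interim analysis with:

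> Comparative interim results will be known only to the DMC and the independent statistician preparing the report. The investigator group will receive a recommendation (continue, modify or stop) without outcome data by arm. Comparative results will be released to it only if the DMC recommends stopping the trial.

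Release should not extend to a recommendation to modify. The trial would then go on with informed investigators, which is the situation to be avoided. The investigator group may keep the final decision on stopping.

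The cost is small: a short change to the protocol, and to the DMC charter if there is one, using the independent DMC and statistician already in place. The downside is that investigators act on a recommendation to continue or modify without seeing the data. One gap remains: if they receive the results after a recommendation to stop and decide to continue, the exposure returns. Such a decision should be documented and reported with the results.
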